#### General trial treatment procedures

Patients included in the trial will be treated according to the department’s standard procedures for surgery, anesthesia, and perioperative care. Type of operation is determined by a well-defined algorithm based on the type of fracture [32]. Standard perioperative care includes D vitamin and calcium supplementation dependent on the patient’s individual level. Further, a standardized liberal transfusion protocol is used with transfusion if hemoglobin (Hb) is < 9.7 g/dl.

After enrollment, patients will be assessed in regard to the study’s primary and secondary outcomes. Thereafter patients are randomized, and the first injection of the trial solution is administered by the dedicated nurse. In case of the primary nurse being absent, a second nurse trained in the protocol will substitute for her.

After discharge, the patient will receive weekly telephone calls from the project coordinator in order to ensure and monitor compliance. The patient will be asked about the amount of consumed nutritional supplement and attendance at physiotherapy sessions. Further, the patient will be asked about their well-being in order to detect potential side effects of the intervention. An interview guide will be used to assure systematic collection of information.

Every 3 weeks, the patient will attend a control visit at the hospital. The dedicated nurse will carry out blood tests and inject the treatment solution according to randomization group. Compliance with the trial as well as outcome/safety parameters will be monitored. Further, the nutritional supplement covering the following 3 weeks will be handed out at the visit.

The intervention period for the nutritional supplementation and exercise intervention is 12 weeks. The patient will receive the last injection at week 12. Further, at the 12-week appointment, an activity monitor will be applied to the patient’s thigh (activPAL; PAL Technologies, Glasgow, UK), which will monitor activity the following week.

Follow-up will occur during week 14, when patients will be assessed according to the primary and secondary outcomes. To ensure that all potential side effects are detected, one last telephone call is conducted during week 16, and thereafter the patient will have no further obligations in relation to the trial. See Fig. 1 for the flow of enrollment and trial-related events.

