#### Secondary outcomes

The following outcomes will be compared between the two groups. Unless stated otherwise, the change in values are measured from baseline until 14 weeks. Figure 2 illustrates time points for assessment of each outcome.
Maximal isometric knee-extension strength (N∙m/kg) in the fractured limb as a percentage of the nonfractured limb. Description of the measurement method is provided under the “Primary outcome” heading.Maximal isometric knee-extension strength (N∙m/kg) in the nonfractured limb. Description of the measurement method is provided under the “Primary outcome” heading.Hand-grip strength in the dominant hand measured using a digital handheld dynamometer (Saehan Grip, DHD-1; Saehan, Changwon, Korea). Hand-grip strength will be expressed in kilograms. A standardized test protocol will be used similar to the one described by Bodilsen et al. [34].Fat mass (total body weight) assessed by dual x-ray absorptiometry (DEXA), expressed in kilograms. DEXA is performed as a whole-body scan and is conducted in accordance with the department’s standard procedures.Bone mineral density (BMD) assessed by DEXA. Registration of total body, total hip, femoral neck, and lumbar spine BMD. Expressed in g/cm^2^. Further T-score is registered. The scan is performed as a whole-body scan and is conducted in accordance with the department’s standard procedures.Lean body mass assessed by DEXA and expressed in kilograms. Registration of total body, legs bilaterally, and arms bilaterally. The scan is performed as a whole-body scan and is conducted in accordance with the department’s standard procedures.Nutritional screening using the Mini Nutritional Assessment–Short Form (MNA-SF). Total score from 0 to 14 points, high scores indicating better nutritional status. The score is frequently used for assessing nutritional status in patients with hip fracture and predicts mortality and readmissions [35, 36].Gait speed is assessed using the 10-m fast speed walking test, standing start. A standardized test protocol is used, and the best result of three trials is reported in meters walked per second (m/s) [28].The Timed Up & Go Test is performed using a four-wheeled rollator and measured in seconds. The patient has to rise from a chair, walk 3 m, turn around, walk back, and sit down [37]. A standardized instruction will be used [38].The de Morton Mobility Index is used for measuring mobility and consists of 15 mobility items ranging from mobility in bed to dynamic balance. The test result is a total score from 0 to 100, with 100 representing the highest level of mobility [39–41].Activity: Sedentary time (lying/sitting), upright time (standing/walking), steps, and transfers is measured using a body-worn accelerometer-based activity monitor (activPAL) [42]. The monitor will be attached to the thigh. The patient will wear the monitor for 1 week from the time point of the 12-week control.Functional level is assessed by the modified New Mobility Score [43–45]. The patients are interviewed about walking ability indoors, outdoors, and when shopping. At baseline, the score refers to the week prior to hospital admission. The total score ranges from 0 to 9. A higher score indicates greater independence.EQ-5D-3L is used for assessing health-related quality of life [46–48] and is administered via interview. At baseline assessment, the score refers to the time prior to the fracture.Hip fracture-related pain at rest and during outcome assessment is evaluated using the Verbal Rating Scale [49]. The patient is asked to rate the intensity of pain in relation to five adjectives: “no pain,” “slight pain,” “moderate pain,” “severe pain,” and “unbearable pain.” The answer is converted to a number between 0 and 4 on an ordinal scale.A global rating of change scale will be used for assessment of patient-perceived change in walking ability during the trial period. Patients will be asked one question related to change in mobility and have five response options ranging from much better to much worse.The Short Falls Efficacy Scale–International is used to measure the patient’s fear of falling (score range from 7 to 28, with higher scores indicating a greater fear of falling) [50, 51]. It is administered as an interview.Fatigue is assessed using the SF-36 (36-item Short Form Health Survey) vitality subscale, consisting of four items related to fatigue/energy [52, 53]. Scores range from 0 to 100 points; high score defines a more favorable health state. Administered as an interview. The baseline assessment refers to the time prior to the fracture.Depression is assessed using the Geriatric Depression Scale, which is administered as an interview [54, 55]. Score range, 0–15. Baseline assessment refers to the time prior to the fracture.Readmissions within 14 weeks will be assessed through the medical journal.Residential status, including home care, will be recorded by interview or medical journal.Mortality will be assessed through the medical journal/Danish civil register.

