### Statistical analyses

Descriptive statistics will be used for presenting baseline characteristics. Continuous data will be examined for normality of distribution using Q-Q plots. Data will be presented as mean (SD) when normally distributed, otherwise as medians (q1–q3) or as frequencies with percentages.

The statistical analysis of the primary outcome will be two-sample *t* test or Wilcoxon rank-sum test as appropriate to determine systematical differences in change scores between the intervention and control groups. For the secondary outcomes, tests will be performed using either chi-square or Fisher’s exact test for categorical data or two-sample *t* test or Wilcoxon rank-sum test for continuous data. Analysis of safety parameters and feasibility endpoints will be descriptive. The level of significance will be set at *P* < 0.05, and confidence intervals (CIs) will be displayed at 95% CI around differences.

The analysis will follow the intention-to-treat principle and include all randomized patients. To create a full analysis set, missing data will be imputed using a multiple imputation technique. Secondary analysis will be conducted for both primary and secondary outcomes on the per-protocol data, where patients are excluded if they are not compliant with the trial. Compliance in relation to per-protocol analysis is defined as 75% intake of nutritional supplement, 75% completed training sessions, and 100% received injections. No interim analyses will be conducted.

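### The per-protocol analysis covers mortality, although a patient who dies before the week-12 injection cannot be in the per-protocol set

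*Protocol article*

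**What the plan says.** The Statistical analyses section makes intention-to-treat on all randomized patients the main analysis and then adds: "Secondary analysis will be conducted for both primary and secondary outcomes on the per-protocol data". Non-compliant patients are left out of that set, and compliance means "75% intake of nutritional supplement, 75% completed training sessions, and 100% received injections".

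The Secondary outcomes section includes two event outcomes that matter here: "Mortality will be assessed through the medical journal/Danish civil register" and "Readmissions within 14 weeks will be assessed through the medical journal". It also includes a third outcome of a different kind: "Residential status, including home care, will be recorded by interview or medical journal". Mortality has no time point of its own, so the section's general rule is taken to apply: "Unless stated otherwise, the change in values are measured from baseline until 14 weeks".

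On dosing, the General trial treatment procedures section says: "The patient will receive the last injection at week 12". The Trial medication section gives injections every 3 weeks from baseline, which makes five.

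The Statistical analyses section makes safety parameters descriptive. That does not exempt mortality, because the Safety parameters section does not list it.

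**The concern.** Compliance is judged over the 12 weeks after randomization, and death during those weeks ends it. The outcome therefore decides who is in the set in which it is counted. Patients in the set are known to have survived to the last injection, so their risk of death is observed only from then on. Whatever the drug does to mortality before week 12, the per-protocol table cannot show it.

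The trial's first hypothesis is that the treatment is feasible and preliminarily safe, and the Discussion says the decision on a confirmatory trial will weigh all the information from the pilot. A per-protocol line with no deaths in either arm could be read as reassurance when it follows from how the set is defined.

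**Working it through.** **Inputs from the article.** Injections at weeks 0, 3, 6, 9 and 12; control visits ±7 days; outcome horizon 14 weeks; 48 patients. The article gives no per-protocol event count to reproduce. Its sample size does reproduce: Lehr's formula gives 16 × (0.22/0.2)² = 19.36, rounded up to 20 per group, and 20 × 1.2 = 24 per group, or 48 in all.

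**Assumptions.** The article gives no mortality rate, so 14-week mortality m of 2%, 5% and 10% is used, with a constant hazard. The injection rule is read as the whole planned course of five.

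**Step 1: the share of deaths that can be counted.** With two weeks left after the last injection, the share is about 2/14 = 14%. If the last injection is given at week 11, the earliest the visit window allows, it is about 3/14 = 21%.

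**Step 2: expected deaths.** Survival to week t is S(t) = (1 − m)^(t/14). Deaths among all randomized patients are 48 × m. Deaths that could be counted per protocol are at most 48 × [S(12) − S(14)]. This is a maximum for a last injection at week 12, because it supposes that every survivor also meets the two 75% rules. The per-protocol risk is [S(12) − S(14)]/S(12).

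| Assumed m | Deaths in 48 randomized | S(12) − S(14) | Most countable per protocol | Share of deaths | Per-protocol risk |
|---|---|---|---|---|---|
| 2% | 0.96 | 0.0028 | 0.14 | 14.2% | 0.3% |
| 5% | 2.40 | 0.0070 | 0.34 | 14.0% | 0.7% |
| 10% | 4.80 | 0.0136 | 0.66 | 13.6% | 1.5% |

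With the last injection at week 11 the shares are 21.3%, 21.0% and 20.6%, so the countable deaths are 0.96 × 0.213 = 0.20, 2.40 × 0.210 = 0.50 and 4.80 × 0.206 = 0.99. In every case, less than one death is expected across both arms.

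**Step 3: readmissions.** Two sessions a week for 12 weeks make 24, and 75% of these is 18, so 6 sessions (3 weeks) may be missed. For the supplement, 25% of 84 days is 21 days. A short readmission, or one after week 12, can therefore stay in the set. Let r be the readmission risk and f the share of readmissions that break compliance. The per-protocol risk is r(1 − f)/(1 − rf). Neither r nor f is in the article. Taking r from 10% to 30% and f from 20% to 80%, the extremes are 0.1 × 0.2/(1 − 0.08) = 2% and 0.3 × 0.8/(1 − 0.06) = 26%. The result lies below r but is not forced near zero.

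**Step 4: residential status.** No compliance rule refers to residence or home care. A patient who moves, or who needs more help at home, can still meet all three rules.

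**The case against.** The strongest reply is that little depends on this table. Intention-to-treat on all randomized patients is the main analysis, so the full death count will stand beside the per-protocol one. Adverse events are recorded to week 16, and their number and severity are a feasibility outcome. Nothing limits either to compliant patients, and no stated decision rests on per-protocol mortality. Entry criteria also select home-dwelling patients without severe heart failure or active cancer, so deaths may be few. All of this stands, and it limits the harm. It gives no reason to produce a table whose result is largely fixed in advance.

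A second reply is that the percentages might be taken over what was due while the patient was alive. The article does not state the denominator. The plain sense of 100% of injections in a fixed five-injection course is all five. If another denominator is meant, it would have to be stated.

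A reader might infer more: that a patient in hospital for a long time cannot be compliant, so that readmissions and residential status are also near zero by construction. The article does not support this. The rules tolerate about three missed weeks of training and supplement, two daily drinks are standard during admission at the unit, inpatient physiotherapy is part of the programme, and control visits may move by 7 days either way. A long readmission makes non-compliance likely, not certain.

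**Conclusion.** The point holds for mortality. As written, the per-protocol mortality comparison leaves out about 86% of 14-week deaths (79% if the last injection is at week 11) because of how the set is defined, so it is uninformative about safety. The percentages rest on a constant hazard and the counts also on the assumed 2% to 10% mortality. The exclusion of every death before the last injection rests on neither, only on reading the injection rule as the full course.

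For readmissions the conclusion is weaker: biased downward, by an amount the article does not allow one to calculate. Residential status is selected on compliance, like the other outcomes, but is not pushed toward zero and needs no exemption of its own. Because the main analysis includes everyone randomized, this is a minor correction.

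**What to change.** In the Statistical analyses section, change the per-protocol sentence to say that mortality and readmissions are analysed in all randomized patients only, with no per-protocol version. Keep the per-protocol analysis for the primary outcome and the other secondary outcomes, including residential status. The compliance definition need not change for this purpose.

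The cost is one sentence. No data, visits, patients or sample size change, and the two tables dropped are one that is close to empty by definition and one with a bias of unknown size.

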### Ethics

The trial will be conducted in accordance with the principles of ICH-GCP and is monitored by the local GCP unit. The protocol is approved by the Capital Regions Research Ethics Committee (H-18004495) and the Danish Medicines Agency (EudraCT identifier 2017-001543-13). The trial is registered with the Danish Data Protection Agency (journal no. AHH-2017-090; I-Suite no. 05980).

All patients enrolled in the trial will have close contact with health professionals through weekly phone calls and hospital visits every 3 weeks. The increased attention, close contact, and strong focus on the individual patient’s well-being can in itself be perceived as positive and thus beneficial. Risks and ARs for study participants are considered to be minimal. Strength training has been widely reported as safe [3, 13, 28, 58], and the planned program ensures a familiarization phase. Occurrence of ARs in relation to trial medication are not expected, owing to the relatively short intervention period and low doses. The safety precautions in the current trial, such as close observations through weekly interviews and assessment of safety parameters every 3 weeks, are considered to be sufficient to minimize risk and discomfort to the patient. However, slight soreness at the injection site could be experienced in relation to blood sampling and injection of trial medication. DEXA scans are conducted at two time points during the trial period. Radiation exposure is minimal, approximately 0.020 mSv corresponding to 1/50th of an X-ray of the lungs, and it constitutes no health risk.

On the basis of available evidence and the safety precautions taken in the present trial, the risk to the exposed patients seems to be absolutely minimal, and we are convinced that this trial is ethical to conduct. The participants do not receive remuneration for participation in the trial.

#### Protocol amendment

The following protocol amendments were approved by the ethics committee (28 September 2018) and the Danish Medicines Agency (26 October 2018):
The inclusion criterion *age* was changed from ≥ 65 years to ≥ 60 years. The cut ≥ 60 years is often used internationally when referring to elderly compared with nonelderly patients with hip fracture [59]. Further, patients from 60 to 64 years old would have the same potential benefit from the intervention.The exclusion criterion concerning *PSA* values was changed, so assessment of PSA is moved to the 3-week control, because a falsely elevated PSA value could be seen during admission due to urine catheterization.The exclusion criterion *terminal illness* was changed to *active cancer or suspected pathological fracture*.The time frame for baseline testing was changed from 6–10 days to 3–10 days due to short hospitalization for some patients.The intramuscular injection of trial medication was described to be administered in the gluteal muscle of the nonfractured leg. Due to difficulties with positioning all patients lying on the side, the description has been changed so that the medication can be administered either in the gluteal muscle or in the rectus femoris

A second protocol amendment concerning extension of the inclusion period until September 2020 has been approved by the ethics committee (27 September 2019) and the Danish Medicines Agency (22 July 2019). The primary investigator and the sponsor will inform the Research Ethics Committee, the Board of Health, and the Data Protection Agency if significant changes in protocol occur.

### Dissemination

Two publications are planned for the HIP-SAP1 trial in peer-reviewed scientific journals. One is the protocol manuscript and the other is the primary trial report concerning feasibility and preliminary effects of the trial. Contributors to the trial will be offered authorship in accordance with the International Committee of Medical Journal Editors guidelines. There is no intention of using professional writers. Trial results will be published regardless of findings being positive, inconclusive, or negative. Further, results will be presented at national and international congresses. Trial participants will be notified of trial results by letter.

## Discussion

Patients with hip fracture are a vulnerable group with high morbidity and mortality. They experience large strength deficits often leading to loss of function and independence. Knowledge regarding interventions enhancing outcome and reducing loss of function in this fragile group will be of immense benefit to both the individual patient in terms of better health and quality of life and the health care system in general.

The HIP-SAP1 trial is, to our knowledge, the first trial investigating the effect of a multimodal intervention consisting of physiotherapy (functional, balance, and strength training), protein-rich nutritional supplementation, and anabolic steroid in rehabilitation following hip fracture surgery. In the literature of rehabilitation following hip fracture, there is a demand for trials exploring the effect of multimodal interventions including muscle-enhancing medicine [6, 13, 21, 24, 25].

This study will contribute useful knowledge about the feasibility, safety, and preliminary effect of such multimodal intervention. If found feasible, this pilot trial will form the basis for a larger confirmatory trial that can finally determine the effect of muscle-building medicine in the rehabilitation of elderly patients with hip fracture, and it will contribute to setting new evidence-based standards for the optimal cross-continuum treatment following hip fracture. Potentially, this will bring a greater proportion of patients back to their previous level of functioning, which might lead to reductions in new falls and fractures, need of home care, and health care costs.

The design of this pilot trial being randomized and blinded, besides clarifying the question of feasibility, will give a preliminary suggestion of effect. Further, the preliminary estimates obtained for outcome parameters in this trial will be used for sample size calculation in a confirmatory trial. Continuing to undertake a larger confirmatory trial will not be based on a statistically significant difference between groups, because the trial is not sufficiently powered, but the results of the tests will be taken into consideration along with an overall assessment of all information provided by this pilot trial.

The intervention being initiated during admission and continued for 12 weeks in the municipality mimics everyday practice, and the physiotherapy intervention is very similar to the existing standard rehabilitation offered by the municipalities, which increases external validity and will ease implementation. In regard to the nutritional component of the intervention, although an important focus area during hospitalization, it is not standard care in the municipalities to receive nutritional supplements for 12 weeks. However, the municipalities are aware of the importance of nutrition in this fragile group of patients. Some municipalities provide protein supplementation for all patients in relation to the exercise session; others conduct nutritional screening as part of the rehabilitation program, and patients in need of supplementation will be seen by a dietitian. On the basis of the current study design, we cannot make recommendations for the use of nutritional supplementation, but we will obtain information on adherence to the nutritional supplement. Knowledge obtained in this trial will inform a definitive trial.

The study is limited by narrow inclusion and exclusion criteria, and recruiting eligible patients might be difficult. The inclusion and exclusion criteria are based on previous studies using anabolic androgenic steroids in elderly patients [60, 61]. Because anabolic steroids are used in a novel field and the population is older and multimorbid, a rather conservative approach has been applied. Further, the criteria are decided on to get a comparable sample without too much “noise” from other factors that could influence outcome. If the trial is feasible and safe, less restrictive criteria might be applied for the larger confirmatory trial. The generalizability of the results of this trial will be limited to a similar population, and therefore the findings will apply only to a smaller proportion of patients with hip fracture.

